### Clinical data collection

The following data will be collected and entered into an online collaborative database:
(1)Basic clinical characteristics: hospital name, patient name, the recorder name, birth date and time, sex, GA, birth weight, height, head circumference, delivery mode, delayed cord clamping time, and Apgar score at 1, 5, and 10 min. Maternal information includes maternal age, race, pregnancy complications, and prenatal glucocorticoid use.(2)Characteristics of cord blood collection, processing, and infusion: the time between collection (birth) and initiation of infusion, cell number before and after processing, cell concentration before and after processing, MNC infusion starting time, MNC infusion duration, infusion volume, infusion cell number per kg, CFU-GM, CD34 + cell count, and cell viability post processing.(3)Co-intervention: respiratory support mode during the first 28 days, 36 GW, and discharge home, respiratory support duration, dose of pulmonary surfactant replacement, postnatal steroid use, surgical closure of PDA, use of blood products, any other surgery, inhaled nitric oxide, and antibiotic administration.(4)Laboratory investigation and image results: peripheral blood glucose before and after infusion, arterial blood gas analysis (PH, PO_2_, PCO_2_) in peripheral blood before and after infusion, serum electrolytes (sodium, potassium, chloride, and calcium), lactic acid, blood urea nitrogen and peripheral blood routine examination (white blood cells, hematocrit, and platelet) during the first 4 weeks of the study, electroencephalogram result, and lung ultrasound during hospitalization.(5)Single-cell RNA sequencing, reactive oxygen species, and inflammatory cytokines (including IL-10, IL-6, IL-1β, and TNF-α) for cord blood and peripheral blood 3–10 days after infusion (samples will be collected from abandoned blood from routine blood tests only if tests are clinically necessary). Single-cell RNA sequencing, reactive oxygen species, and inflammatory cytokine results between cord blood cells and peripheral blood 3–10 days after intervention in each patient and single-cell RNA sequencing, reactive oxygen species, and inflammatory cytokine results of peripheral blood 3–10 days after intervention between placebo and MNC infusion groups is compared to analyze the therapy-induced molecular signal and immune alteration, therefore exploring the underlying mechanisms of the protective effect of ACBMNC on BPD.

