Both genetic predisposition and intervention difference between individuals affect the clinical outcomes of patients (6, 22). To increase the statistical potency of the therapeutic effect of cord blood stem cells especially among small sample trials, enrolling very preterm monozygotic twins of less than 32 gestation weeks (GW) could improve the comparability between intervention and control groups as the hereditary material is the same within monozygotic twins.

With these concepts in mind, here, the authors will enroll very preterm monozygotic twins and assign the random number. Therefore, one of the twins will be assigned to the control group and the other to the intervention group. Furthermore, we will perform single-cell RNA sequencing for cord blood cells and blood cells 3–10 days after intervention and detect whether reactive oxygen species and inflammatory cytokines are present in serum from abandoned blood samples. As the genetic background is the same within monozygotic twins, the results of single-cell RNA sequencing are expected to have better comparability, following which the mechanisms elucidated will reveal the effect of autologous cord blood mononuclear cell (ACBMNC) infusion to the maximum (23). This will be the first randomized, placebo-controlled, and double-blinded trial to evaluate the efficacy of ACBMNC infusion as a prophylactic measure for BPD in monozygotic twin premature infants who have the same genetic background and investigate the underlying protective mechanisms *via* single-cell RNA sequencing.

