## Intervention

### Enrollment and umbilical cord blood collection and transportation

Written informed consent is obtained from the parents or guardians of all infants before delivery. For each monozygotic twin, neonatologists will be summoned at least 1 h before delivery, and their brief is to study patient data and confer with the obstetrician to verify whether the patients fulfill the enrollment criteria. An intrahospital transport team will be organized, which includes three neonatologists (one of them will be a senior physician). A transport incubator and ventilator with an air oxygen mixer and heater humidifier that can provide intermittent positive-pressure ventilation will be equipped for intrahospital transport from the delivery suite to the NICU in the same hospital (Figure 2C). Two blood-collection bags (WEGO, China) containing 28 ml of citrate-phosphate-dextrose anticoagulant and several blood-collection tubes are prepared.

After the neonates are delivered, delayed cord clamping is done for 30–60 s if the babies do not show severe asphyxia and do not need immediate resuscitation. After the twins are born and before the placenta is delivered, both umbilical veins are sterilized and then punctured with a 17-gauge needle. A part of the cord blood will be collected to the blood-collection tubes for clinical blood tests and single-cell RNA sequencing within 24 h after collection, and then cord blood is collected using a blood-collection bag (WEGO, China) by trained medical staff (Figures 2A,B).

Enrollment will be evaluated again by the neonatologists according to the inclusion and exclusion criteria. The blood-collection bag is closed and sealed after the collection is completed. The cord blood bag is labeled with the full name of the neonate, the hospital name, and the birth time and then placed in a cord blood storage container at 4°C storage and sent to the GDCBB within 2 hours. The GDCBB is a provincial, public cord blood bank with the clinical certification of the American Association of Blood Bank (AABB) and authentication of the Chinese Ministry of Health. The GDCBB has been equipped with a thermostat that is specifically used for cord blood transportation; it is able to maintain a temperature of 4°C during transportation. The transportation time duration (both from and back to the hospital) is within 2 hours depending on the traffic condition.

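### Mechanistic blood is available only when a test was clinically needed, and the stated contrasts leave out the co-twin pairing and the cord-blood baseline, so the therapy-induced reading is not secured

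*Protocol article*

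**What the plan says.** Clinical data collection, item 5, covers single-cell RNA sequencing, reactive oxygen species and four named cytokines. On the later blood it states that "samples will be collected from abandoned blood from routine blood tests only if tests are clinically necessary". The Introduction gives the same source for the serum markers.

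The cord-blood sample is not tied to a later clinical test. Under Enrollment and umbilical cord blood collection and transportation, tubes are filled at birth, before any infusion.

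Item 5 then names two comparisons. One is "between cord blood cells and peripheral blood 3–10 days after intervention in each patient". In the other, "peripheral blood 3–10 days after intervention between placebo and MNC infusion groups is compared". Both are given one purpose: the material "is compared to analyze the therapy-induced molecular signal and immune alteration".

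Statistical analysis prescribes an unpaired Student's t-test between the two groups for continuous variables. It names no within-pair or baseline-adjusted analysis. Yet the Introduction justifies the twin design partly because "the results of single-cell RNA sequencing are expected to have better comparability". The work is item 7 of the Secondary objectives but does not appear under Outcome measures.

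**The concern.** There are three separate weaknesses.

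1. **Selection after randomisation.** Whether an infant supplies day 3–10 blood, and when, follows its clinical course. Safety monitoring and co-intervention gives a concrete link: blood gases are taken at least daily until the infant is weaned from ventilation, and ventilation duration is an outcome the trial compares. If the infusion alters that course, it also alters who is sampled.
2. **A within-infant contrast read as a treatment effect.** Cord blood and peripheral blood several days later differ in postnatal age and in source as well as in treatment.
3. **A between-arm contrast that does not use the design.** It is stated on post-infusion values only. The general unpaired test treats co-twins as independent although allocation is within pairs.

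At stake is the mechanistic conclusion: a real effect could look smaller than it is, and postnatal change could be taken for therapy. The primary outcome, safety monitoring and sample size are not affected.

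**Working it through.** The article states no sample size, effect size or sampling rate for this work, so there is no figure to reproduce. All inputs below are assumptions except the 60 pairs.

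**Selection.** Simulation of 400,000 pairs: marker SD 1, true effect −0.50 SD, cord-blood values correlated 0.5 between co-twins, own cord-to-later correlation 0.5. The probability of being sampled is logistic in the day 3–10 marker, with intercept 0.85.

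| Slope | Sampled, control / treated | Unadjusted | Adjusted for own cord blood | Complete pairs, within-pair |
|---|---|---|---|---|
| 0 | 70% / 70% | −0.50 | −0.50 | −0.50 |
| 0.5 | 69% / 64% | −0.47 | −0.48 | −0.48 |
| 1 | 67% / 57% | −0.42 | −0.44 | −0.43 |
| 2 | 63% / 48% | −0.33 | −0.36 | −0.34 |

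With own cord-to-later correlation 0.8, the adjusted estimates at slopes 0.5, 1 and 2 are −0.49, −0.47 and −0.42. With no treatment effect, and hence no change in who is tested, differences stayed within 0.01 of zero at every slope.

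A sharper rule gives more attenuation. Suppose treatment lowers severity by 0.5 SD, severity and marker correlate 0.6, and only infants above a severity cut-off c are sampled. The observed difference is 0.6 × {[−0.5 + φ(c+0.5)/(1−Φ(c+0.5))] − φ(c)/(1−Φ(c))}.
- 80% of controls sampled (c = −0.84): 63% of treated sampled, and 0.6 × (0.094 − 0.350) = −0.15 against a true −0.30.
- 90% of controls sampled (c = −1.28): 78% of treated sampled, and 0.6 × (−0.124 − 0.195) = −0.19.

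So the loss runs from nothing to about half, depending wholly on the assumptions.

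**Complete pairs.** If each infant is sampled independently with probability s, pairs with both twins sampled number 60s²: 15 at 50%, 29 at 70%, 49 at 90%.

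**Standard error.** At s = 0.70 there are 42 infants per arm and 29.4 complete pairs. With marker SD 1 and co-twin correlation ρ in the day 3–10 marker:
- variance assumed by the unpaired test: 2/42 = 0.0476;
- true variance of that mean difference: 2/42 − 2ρ × 29.4/42², which is 0.0376 at ρ = 0.3 and 0.0310 at ρ = 0.5;
- overstatement of the standard error: √(0.0476/0.0376) = 1.12 and √(0.0476/0.0310) = 1.24.

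With every pair complete the factor is 1/√(1−ρ), or 1.20 and 1.41.

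**What within-pair analysis buys.** Complete pairs alone give variance 2(1−ρ)/29.4, or 0.0476 at ρ = 0.3 and 0.0340 at ρ = 0.5. Both exceed the true variance of the all-infant difference, because single-twin samples are discarded. Pairing therefore mainly corrects the standard error. Adjustment for cord blood is what reduces the variance, by the factor 1 − r², where r is the correlation between within-pair differences at baseline and follow-up: 0.91 at r = 0.3 and 0.75 at r = 0.5.

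**The case against.** The strongest reply is that treatment is randomised within pairs, so leaving out a baseline term costs precision and not validity. The slope 0 row confirms this, and the point stands. A reader might infer that the mechanistic comparison cannot isolate a therapy effect at all because it never adjusts for cord blood. The documents do not support that: cord blood is collected and compared, and the between-arm contrast is distorted only if treatment changes who is tested. Nor do they show that the sicker twin, or the control arm, will in fact be sampled more. That is plausible but not established.

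Next, the within-infant comparison includes placebo infants, whose change from cord blood shows maturation without therapy. This is fair. What is missing is any stated contrast of that change between arms.

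Third, models for exploratory markers are often left to an analysis plan that is not shown here, and Statistical analysis does not name these markers. This stands for model detail. But the article itself fixes the sampling rule, the two comparisons and a general unpaired test, and no later plan can recover blood that was never kept.

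Fourth, routine blood examinations are recorded for the first 4 weeks. If all infants happen to be tested in days 3–10, selection is small. No schedule is given, so this cannot be settled. For the same reason, same-day samples from both twins without an extra draw cannot be assumed.

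**Conclusion.** The point holds in limited form. Sampling is decided after randomisation. If the infusion changes clinical course, the arms may contribute different infants and a real effect may be attenuated, by an amount the documents cannot fix. Change from cord to peripheral blood within infants cannot alone support a therapy-induced reading. The between-arm comparison is stated on post-infusion blood alone, and the unpaired test misstates the standard error, overstating it when co-twins correlate positively.

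Baseline adjustment and pairing lessen the selection bias but do not remove it. Because the work is described as exploring mechanisms and is not a listed outcome, this is a worthwhile and inexpensive correction and not a threat to the trial's main result.

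**What to change.** - Make the main mechanistic contrast the within-pair difference (MNC twin minus placebo co-twin) in day 3–10 values, adjusted for each twin's own cord-blood value where available. Contrasting the change from cord blood between co-twins serves the same purpose.
- Present change from cord to peripheral blood within an arm as descriptive, not as evidence of therapy.
- Where leftover blood exists for both twins, use the samples closest in time.
- Report number, timing and proportion sampled by arm, and the number of complete pairs.
- Label the result exploratory.

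The cost is analysis and reporting wording, with no additional blood required. Pairs with one sampled twin leave the main contrast, but a mixed model with a pair effect can retain them, which matters given the complete-pair counts above. A cord-blood value is not assured for both twins, since Inclusion criteria (item 9) and Cord blood processing allow enrolment when only one has enough cord blood. Some residual selection will remain.

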### Outcome measures

Primary outcome:
– Surviving without BPD.Secondary outcomes:
– Surviving without severe preterm-associated complications (severe BPD, severe ROP, and severe IVH).– Mortality rate.– BPD severity.Other outcomes:
– Incidence of other preterm complications including IVH, PVL, NEC, ROP, RDS, VAP, LOS, and anemia.– Duration of mechanical ventilation and oxygen therapy.– Frequency of re-intubation.– The time (days) to return to BW.– Body weight during the first 4 weeks (measured on each week).– Duration of hospitalization.– Hospitalization expenses.We will use the following clinical definitions in this study: (all clinical diagnoses will be defined according to a standard reference) (30).
1.GA will be determined on the basis of a combination of the last menstrual period and early ultrasound findings.2.The diagnosis of common preterm complications will include the following:
BPD, defined as treatment with oxygen >21% for at least 28 days, and its severity will be assessed at 36 weeks of postmenstrual age or discharge home, whichever comes first. Mild BPD is defined as breathing room air at assessment. Moderate BPD is described as the need for <30% supplemental oxygen, and severe BPD is described as needing ≥30% supplemental oxygen or positive airway pressure. For these patients, BPD status will be analyzed by a committee of three independent experts blinded to the study group.RDS will be defined if the infants show evidence of respiratory symptoms such as grunting and chest retraction, typical chest radiography findings, and/or treatment with surfactant, and the need for assisted ventilation.NEC will be defined using Bell's classification. Infants with stage II or above will be diagnosed with NEC.LOS will be defined if the infants report positive bacterial culture results after the first 72 h of birth.ROP will be defined according to the International Classification for Retinopathy of Prematurity. Severe ROP is defined as ROP needing surgical treatment.Anemia is defined as hemoglobin of no more than 140 g/L.IVH and PVL will be defined by serial head ultrasound, performed according to the description by Volpe. The first head ultrasound will be performed within 3 days after birth and follow-up head ultrasound examinations will be performed every week until the day of discharge. Severe IVH is defined as ≧stage 3 IVH.VAP is defined as a pneumonia occurring after the patient has been intubated and has received mechanical ventilation for more than 48 h.

### Follow-up

All infants will be followed up three times (corrected GA of 40 weeks and corrected age of 12 and 24 months), and the following parameters will be recorded.

*Follow-up content at corrected GA of 40 weeks:*
– Main caregiver and the education level.– Smoking in main caregivers.– Feeding mode (breastfeeding, formula, and mixed feeding).– Anthropometric characteristics: weight, length, and head circumference.– Respiratory outcomes: the occurrence of wheezing, supplemental oxygen requirement, and rehospitalization because of pneumonia.– Neurodevelopmental outcome: neonatal behavioral neurological assessment score, the occurrence of seizure, encephalomalacia, intracranial hemorrhage, and auditory and visual impairment.– Results of blood routine examination.*Follow-up content on corrected age of 12 and 24 months:*
– Anthropometric characteristics: weight, length, head circumference, and anterior fontanel size.– Respiratory outcomes: the occurrence of wheezing, asthma, nocturnal cough, supplemental oxygen requirement, and rehospitalization because of pneumonia.– Degree of neurodevelopmental impairment *via* standardized neurological examination (using the Bayley scales) and other major neurodevelopmental outcomes such as cerebral palsy, seizures, auditory impairment, and visual impairment.– Results of blood routine examination.

### Statistical analysis

Mean and standard deviation are reported for continuous variables, and the number and percentage are reported for categorical variables. Group comparisons of categorical variables for outcomes and co-interventions including death, BPD, and BPD severity are performed using nonparametric tests, the Fisher's exact test, or chi-square test, as appropriate. The relative risk (RR) is calculated as the ratio of the cumulative incidence rates of an event occurring in the intervention infusion group to the control group, and the number needed for treatment as the inverse of these two cumulative incidence rates. The results are shown as RR with 95% confidence interval (CI). For continuous variables, the mean values at each time point in each group of the variables are derived from a generalized linear model and the differences in the values over time are compared using an unpaired Student's t-test between the two groups. Kaplan–Meier cumulative incidence plots are generated to show time-to-event end points, namely, extubation and weaning to room air. All statistical tests are two-tailed, and *p*-values < 0.05 are deemed statistically significant. The Breslow–Day test and Cochran–Mantel–Haenszel (CMH) test will be used to adjust the data derived from different participating centers. The results will be reported as odds ratio (OR) with 95% CI. All statistical tests will be two-tailed and a *p*-value < 0.05 will be considered statistically significant. All statistical analysis will be performed using SPSS 21.0 (IBM).

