## Methods

### Study design and settings

This study protocol describes a randomized, placebo-controlled, double-blinded, and multicenter trial to be conducted at seven medical centers (Guangdong Women and Children Hospital, Dongguan Maternal and Child Health Hospital, Zhongshan Boai Hospital, Shunde Hospital-Southern Medical University, Dongguan Hospital-Southern Medical University, Nanfang Hospital-Southern Medical University, and Affiliated Maternal and Child Hospital of Foshan-Southern Medical University) in tertiary hospitals. The participating NICUs are selected by an expert committee based on the distance to the Guangdong Cord Blood Bank (GDCBB) and the level of intensive care that these NICUs could provide. The Guangdong Cord Blood Bank is a public provincial blood bank affiliated with the Guangdong Women and Children Hospital and collects cord blood routinely at these enrolled hospitals. To ensure that the cord blood is processed and infused to infants within 24 h after birth, the distance between these centers should be short. Furthermore, to reduce the differences in therapeutic treatment between the selected centers, a uniform guideline regarding the treatment of patients has been devised in all clinical centers. These centers hold quality control meetings every 3 months to ensure research consistency and report and analyze the possible side effects caused by MNC infusion. In this study, a total of 60 pairs of monozygotic twin premature infants fulfilling the eligibility criteria will be enrolled. For each pair, one random number will be assigned to the first baby of the twins; if the last digit of this random number is odd, the first baby will be assigned to the intervention group, and the second baby will be automatically assigned to the control group; in contrast, if the last digit of this random number is even, the first baby will be assigned to the control group, and the second will be automatically assigned to the intervention group. The protocol for this study has been developed based on the Standard Protocol Items: Recommendations for Interventional Trials (SPIRIT) checklist (Supplementary material S1, S2). We have followed the Consolidated Standards of Reporting Trials (CONSORT) guidelines and the study design is illustrated in Figure 1.

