### Randomization

The randomization sequence will be generated electronically using SPSS (version 21). Following enrollment, the subjects will be assigned to treatment levels or groups after the verification of their eligibility and consent status. A random number will be assigned by computer for each pair of enrolled twins. For each pair, one random number will be assigned to the first baby of the twins; if the last number of this random number is odd, the first baby will be assigned to the intervention group, and the second baby of the twins will be automatically assigned to the control group; in contrast, if the last number of this random number is even, the first baby of the twins will be assigned to the control group, and the second will be automatically assigned to the intervention group. Those enrolled in the ACBMNC group will receive an infusion of ACBMNC within 24 h after birth. Those in the placebo group will receive an infusion of a placebo solution consisting of normal saline with similar volume based on the cell number results in their cord blood after processing. The ell dose for all patients will be 5 × 10^7^ cells per kilogram (18, 27).

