Our clinical studies and those of others have shown that cord blood-derived stem cell application is both safe and effective in the prevention of BPD in very preterm neonates (18–20, 27). Stem cells play a vital role in lung development, and their use for preventing or treating BPD has emerged as a promising therapy (15–21, 23, 27). However, the genetic heterogeneity between control and intervention groups may decrease the comparability between these groups, thereby reducing the statistical power of the therapeutic value of cord blood stem cells, especially in small sample trials (22). As various factors affect the complex molecular signals involved in the developing lung, the pathophysiological basis for BPD is manifold (6, 7). In this study, the intervention time point is the first 24 h after birth; our aim is to observe the preventive effect on BPD, and we will keep the postnatal medical treatment of twins to the maximum consistent according to the centers’ guideline. Furthermore, in the exclusion criteria, twins diagnosed with twin-to-twin transfusion syndrome confirmed by prenatal ultrasonography are also excluded. All these measures aim to minimize the environmental impact on the results. Genetic susceptibility to BPD is suggested by several studies on twins (22, 34), and there is an ongoing search for the role of genetic susceptibility to BPD (22, 35–37). Although in randomized control trials, baseline characteristics could be standardized or corrected for, it is difficult to evaluate or correct genetic predisposition. To treat very preterm monozygotic twins randomly could make the genetic predisposition distribution as similar as possible in two groups. As we know, monozygotic twins are regarded as the best research objects in clinical studies (38). Similar to a single-birth patient study, the different environment exposures or different growth rates will be balanced by the randomization and double-blinded characteristics between groups. As the genetic background in monozygotic twin premature infants is the same, the random enrollment of each of the twins in the placebo and MNC intervention groups will reduce the interference of genetic difference on assessing the protective effect of MNC on lung development and the outcome of BPD. This contributes to enhancing the statistical power of the therapeutic effect of cord blood stem cells and reducing the required sample size.

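### The tests named for comparing the arms ignore the twin pairing, so with positive within-pair correlation they are conservative and forgo much of the precision claimed for the design

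*Protocol article*

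**What the plan says.** Allocation is by pair. The Randomization section of the protocol article states: "A random number will be assigned by computer for each pair of enrolled twins". Under Study design and settings, when the number is odd, "the first baby will be assigned to the intervention group, and the second baby will be automatically assigned to the control group"; when it is even, the roles are reversed. The Introduction puts it generally: "one of the twins will be assigned to the control group and the other to the intervention group". The planned size is 60 pairs.

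The Statistical analysis section then names these comparisons:

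- Categorical outcomes, including death and BPD: unspecified nonparametric tests, Fisher's "exact test, or chi-square test, as appropriate".
- Continuous outcomes: group means come from a generalized linear model, and "differences in the values over time are compared using an unpaired" Student's t-test.
- Centre: the Breslow–Day and CMH "test will be used to adjust the data derived from different participating centers".
- Relative risks and odds ratios with 95% intervals, with no mention of the pair.

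The Discussion gives two reasons for enrolling monozygotic twins. One is that genetic predisposition is balanced between the arms. The other is a gain in power and "reducing the required sample size".

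**The concern.** The data will be 60 matched pairs, but each test named for comparing the arms is built for two independent samples. The variance of a difference between matched infants contains a covariance term, and these tests set it to zero. If co-twins tend to share the outcome, the standard error used is larger than the true one.

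CMH by centre does not repair this. Both twins of a pair belong to one centre and sit in opposite arms, so the arms are already balanced within every centre. The stratification can take up only the part of the within-pair likeness that is due to centre, not the part due to shared genes and gestation.

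At stake is precision on the primary outcome. The Introduction says that earlier trials were small and found no significant difference on their main outcomes. An analysis that gives up precision makes that result more likely here, and the same holds for deaths and complications.

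**Working it through.** **Inputs from the protocol article:** 60 pairs; control rate pA = 0.30 and power 80% (Sample size); two-sided significance at 0.05 (Statistical analysis).

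**Reproducing the plan's own figure.** The Sample size formula with pA = 0.30, pB = 0.10, a 1:1 ratio and two-sided alpha 5% gives

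n = (0.21 + 0.09) × ((1.960 + 0.842) / 0.20)² = 58.9, so 59 per group against the stated 60.

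The stated number therefore rests on an absolute drop of 20 points and on alpha of 5%. (The printed 0.05% would give 141 per group, and a relative 20% reduction 856; those are separate matters.) The formula is for independent groups and contains no pairing term.

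**Assumption.** The documents give no within-pair correlation φ. I use 0 to 0.5. The upper end is close to the largest value possible for rates of 0.30 and 0.10: (0.10 − 0.03) / √(0.21 × 0.09) = 0.51.

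**Standard error of the risk difference.**

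- Unpaired: √(0.30 / 60) = 0.0707 at every φ.
- Paired: √((0.30 − 2φ√(0.21 × 0.09)) / 60), where √(0.21 × 0.09) = 0.1375.
- At φ = 0.3: √((0.30 − 0.0825) / 60) = 0.0602, and 0.0707 / 0.0602 = 1.17.

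**True error and power.** These come from exact enumeration of all outcomes of 60 pairs, at nominal two-sided 5%, with chi-square uncorrected for continuity. True error is at 30% versus 30%; the SE excess and power are at 30% versus 10%.

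| φ | Unpaired SE too large by | True error: chi-square | Fisher | mid-p McNemar | Power: chi-square | Fisher | mid-p McNemar | exact McNemar |
|---|---|---|---|---|---|---|---|---|
| 0 | 0% | 5.3% | 3.1% | 4.4% | 80.2% | 73.0% | 78.6% | 72.7% |
| 0.1 | 5% | 4.1% | 2.3% | 4.5% | 81.5% | 74.1% | 83.1% | 77.5% |
| 0.2 | 11% | 3.0% | 1.6% | 4.6% | 82.9% | 75.3% | 87.5% | 82.4% |
| 0.3 | 17% | 2.1% | 1.0% | 4.7% | 84.5% | 76.7% | 91.8% | 87.5% |
| 0.5 | 36% | 0.65% | 0.25% | 4.4% | 88.7% | 80.4% | 99.4% | 98.4% |

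**Continuous outcomes.** With equal variances in the two arms, the unpaired standard error is too large by the factor 1/√(1 − ρ), where ρ is the within-pair correlation. That is 1.20 at ρ = 0.3 and 1.41 at ρ = 0.5.

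**The case against.** Four points can fairly be made for the plan.

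1. **The tests are consistent with the sample size.** The only power figure in the document is 80%, from an independent-groups formula, and chi-square delivers it at every correlation (80.2% rising to 88.7%). This stands. A reader might infer that the trial is underpowered or that the benefit of twins is lost altogether; the figures do not support that. Fisher does give only 73% to 80%, but it is already at 73% with zero correlation, so pairing is not the cause of that shortfall.

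2. **Genetic balance is kept.** Within-pair allocation secures it whatever test is used. This stands too. The criticism applies to the Discussion's claim about power and sample size, not to its claim about comparability.

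3. **The error is on the safe side.** A reader might take a wrong standard error to mean excess false positives. With positive correlation the opposite holds: a significant result would stand, and with complete pairs the estimated risk difference is unchanged.

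4. **Not everything in the section is unpaired.** The nonparametric tests are unspecified and could include a paired one, no pair term is either stated or ruled out for the generalized linear model, and no test is attached to the Kaplan–Meier plots. The point therefore covers the tests that are named, not every analysis.

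An unseen analysis plan does not answer the point, because the article itself fixes the unpaired t-test, chi-square and Fisher; a plan with paired methods would contradict it.

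**Conclusion.** The point holds in this form: allocation is within pairs, and the tests named for comparing the arms treat them as independent. With positive correlation the result is conservative inference and forgone precision, not an invalid positive claim.

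The size depends on a correlation that the documents do not give. At 0 there is no loss, and mid-p McNemar is then slightly the weaker test. At 0.1 the gain from pairing is under 2 points of power. At 0.2 to 0.3 it is about 5 to 7 points over chi-square and about 12 to 15 over Fisher, and the unpaired interval is 11% to 17% too wide. The figures at 0.5 are near the ceiling and should not be read as expected values. The direction rests on the correlation being positive, which the article's own argument from genetic susceptibility presumes. The power figures also assume the 30% to 10% drop that reproduces the sample size.

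**What to change.** - **Primary and other binary outcomes:** replace chi-square/Fisher and CMH by centre with mid-p McNemar, or with conditional logistic regression or CMH stratified by pair. Report a matched-pair risk difference and risk ratio with 95% intervals. Centre needs no separate adjustment, since it is constant within a pair.
- **Exact McNemar is not an equal substitute.** Its true error is only 2.5% to 3.0%, and its power is below that of chi-square at correlations of 0 to 0.2.
- **Continuous outcomes:** replace the unpaired t-test with a mixed model that has a random effect for pair, and one for infant where measures repeat. This keeps pairs in which one twin's value is missing, for example after a death or loss to follow-up. A paired t-test serves where both values are observed.
- **Sample size section:** state that 60 pairs was derived without using the pairing, so that the Discussion's claim of a smaller sample is not read as having been applied.

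The cost is wording and a little more analysis work, with no extra patients or data. The downside is slightly lower power if the correlation is near zero (78.6% against 80.2%). The change should be made before unblinding, so that the choice of test cannot be driven by the data.
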